#### Screening visit

The following screening examinations will be conducted before the surgery visit (days (D)–30 to D0): 1) measurement of CMT using optical coherence tomography (OCT); 2) measurement of visual acuity (using the Early Treatment Diabetic Retinopathy Study (ETDRS) scale), a basic visual function parameter; 3) measurement of IOP, as hypertension is a major complication of peri- and intraocular corticosteroid injection; 4) examination of the anterior segment by slit lamp (SL) to quantify the flare and assess the clarity of the lens since the second most common complication of peri- and intraocular corticosteroids is development of a cataract; 5) examination of the posterior segment (fundus) and nonmydriatic fundus photography to assess vitreous haze; 6) examination of fluorescein angiography to detect vasculitis, an associated papillitis; 7) automated quantitative and objective measurement of the flare when available using a laser flare meter (LFM), which enables a more accurate assessment of the status and previous inflammatory condition of the blood–aqueous barrier (reference value); 8) measurement of blood pressure, as systemic corticosteroids can induce hypertension and the pathways around the eyes especially mean that treatment is not purely local (exclusion criterion); and 9) blood tests for fasting plasma glucose and glycohaemoglobin (because systemic corticosteroids can induce diabetes and, more importantly, the pathways around the eyes mean that treatment is not purely local; and exclusion criterion). In addition, a pregnancy test (beta human chorionic gonadotropin) will be conducted for women of childbearing age; pregnant women are excluded from the protocol even though peri- and intraocular corticosteroids are permitted during pregnancy. Finally, a serology test will be made for HIV, hepatitis B and C virus, TPHA-VDRL and Quantiferon if the status is unknown to eliminate macular oedema due to infection and systemic infectious diseases at risk of aggravation by treatment with corticosteroids, with the exception of obvious postoperative inflammation.

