### Objectives and statistics

#### Objectives

The main objective of our study is to evaluate the efficacy of subconjunctival injection of triamcinolone in reducing CMT measured by OCT, the most objective, relevant and noninvasive criterion, compared with intravitreal injection of a dexamethasone 700 μg implant which has been approved for this indication, between the inclusion visit and 2 months after treatment (M2 visit).

The timeframe was chosen based on data from the Huron study of Ozurdex® [17, 24, 25] and data from our retrospective study on triamcinolone in the department at CHU Nantes [22].

The secondary objectives are: 1) evaluation of the experience of the injection; 2) evaluation of the effectiveness of the injection studied at each visit, measured by the gain in visual acuity (by the EDTRS scale; a key parameter of visual function), the reduction in flare and vitreous haze which are quantifiable ocular inflammatory parameters measured using an SL and LFM in centres equipped with this technology, the CMT measured using OCT (enabling evaluation of the duration of action of a subconjunctival triamcinolone injection compared with an intravitreal injection of a dexamethasone 700 μg implant; the duration of action of the injection is determined by the reappearance of oedema), the local and general tolerance of the two methods (collecting details of all AEs/SAEs) and the patients’ quality of life; and 3) economic evaluation of the efficiency (cost–utility analysis) of the subconjunctival triamcinolone injection compared with intravitreal injection of a dexamethasone implant from a societal perspective and over a 6-month period.

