#### Secondary outcomes

Secondary outcomes of the study are: 1) the scoring of “the moment” of injection on the day of injection (tolerable, uncomfortable, very unpleasant) and the rating on a visual analogue scale (from 0 cm = no pain to 10 cm = extreme pain); 2) visual acuity (ETDRS scale) at every visit to determine the gain between the inclusion visit and the follow-up visits (the mean scores for each arm will be compared at each follow-up visit); 3) the flare (using SL and LFM if available) at every visit to determine the reduction between the inclusion visit and the follow-up visit (the mean scores for each arm will be compared at each follow-up visit); 4) the vitreous haze at every visit to determine the reduction between the inclusion visit and the follow-up visit (the mean scores for each arm will be compared at each follow-up visit); 5) the thickness of the central macula of the treated eye to determine the duration of action at every visit (as stated in the objectives, the duration of action of the injection is determined by the reappearance of oedema; the mean scores for each arm will be compared at each follow-up visit); 6) AEs/SAEs including intermittent ocular hypertension, cataract, endophthalmitis, glycaemic and blood pressure imbalances at every visit; and 7) EQ-5D questionnaire on patient quality of life at every visit.

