#### Measures used to determine the outcomes

OCT is used to accurately visualise the different layers of the retina, including the macula, using an infrared laser. This is a contactless examination which is noninvasive, painless and brief.

An LFM is a device used to measure the protein concentration in the anterior chamber using a helium–neon laser. This is a contactless examination that is non-invasive, painless and brief.

All the ophthalmic examinations performed at inclusion and during follow-up are common practice in ophthalmology. The visual acuity, IOP, examination using the SL and fundus examination form the basis of all clinical ophthalmic examinations. OCT is the test of choice for characterising and quantifying macular oedema, irrespective of type. This testing is contactless and is noninvasive, painless and brief. The values considered to be normal are: visual acuity, ETDRS 100; IOP, 12–21 mmHg; LFM, no proteinic flare or cellular Tyndall; fundus, no cellular Tyndall or vitreous haze; macula as described, normally LFM <10 ph/ms, CMT <300 μm and >250 μm.

The patient will be given the EQ-5D questionnaire validated in France [28, 29] at each visit to measure their quality of life. The EQ-5D consists of a questionnaire and a visual analogue scale. The questionnaire focuses on five areas: mobility, personal autonomy, current activities, pain/discomfort and anxiety/depression. There are three possible answers for each of these dimensions (EQ-5D-3 L), thus allowing for 243 health states. QALYs will be calculated for each arm using area under the curve methodology and the weighting coefficients available in France for the EQ-5D-3 L [29, 30].

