For secondary end points, the mean visual analogue scale score evaluating the moment of injection will be compared between groups using a linear mixed model; the score for the moment (tolerable, uncomfortable or very unpleasant) will be compared using the Mantel–Haenszel stratified Chi-squared test. A linear mixed model will be used to compare the change in ETDRS from D0 to 6 months between the groups. SL and LFM between D0 and 2 months will be compared between the groups using nonparametric Van Elteren tests (semiquantitative outcome). Duration of injection efficacy (duration is determined by the reappearance of oedema) will be compared between the groups using the Van Elteren test (semiquantitative outcome). Descriptions of AEs/SAEs will be reported in the two groups. Comparisons between the groups will be performed using Chi-squared or Fisher tests for intermittent ocular hypertension, cataract, endophthalmitis, glycaemic and blood pressure imbalances in both arms. There will be no imputation for missing data for these secondary end points.

For the economic assessment, mean costs and their corresponding 95% CIs will be presented. The ICERs will be estimated along with their corresponding acceptability curves, i.e. the curves indicating the probability that an intervention is cost effective conditional on society’s willingness to pay for an additional unit of effectiveness (i.e. an additional QALY gained) and considering the sampling uncertainty around the estimated ICERs.

As costs and ICERs are not normally distributed, the 95% CI and the cost-effectiveness acceptability curves will be determined using the nonparametric bootstrap resampling technique.

Sensitivity analyses will be performed for all end points, adjusted for the duration of macular oedema. All statistical tests will be bilateral. For secondary endpoints, a *P* value less than 0.05 will be considered statistically significant. Analyses will be performed using SAS statistical software (SAS Institute Inc., Cary, NC, USA).

As this is a noninferiority study, the analyses will be carried out on the intent-to-treat population and on the per-protocol population. The intent-to-treat population consists of all randomised patients in the study. The per-protocol population includes the most compliant patients, based on compliance with the inclusion and exclusion criteria, absence of major deviations from the protocol and availability of the main criterion.

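### Laser flare, a quantitative measure, shares the semiquantitative rank test of change planned for slit-lamp flare, so its baseline is not used as a covariate

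*Protocol article*

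**What the plan says.** Three parts of the protocol article describe laser flare as a measured quantity.

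- Screening visit: "automated quantitative and objective measurement of the flare when available using a laser flare meter (LFM".
- Measures used to determine the outcomes: "An LFM is a device used to measure the protein concentration in the anterior chamber". The same section gives a numeric reference value, "normally LFM <10 ph/ms".
- Objectives: flare is "measured using an SL and LFM in centres equipped with this technology", so laser readings will exist for only some patients. The number of equipped centres is not stated.

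Statistical methods then handles both flare measures in one sentence, which compares slit-lamp and laser flare from D0 to 2 months by "nonparametric Van Elteren tests (semiquantitative outcome". It names no baseline covariate for flare. For the primary endpoint, the same section log-transforms CMT and fits a mixed linear model with centre as random effect and the D0 value as covariate.

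Secondary outcomes defines the flare endpoint through its visits, "to determine the reduction between the inclusion visit and the follow-up visit", and adds that "the mean scores for each arm will be compared at each follow-up visit".

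**The concern.** A slit-lamp flare grade is ordinal, and a centre-stratified rank test suits it. A laser reading in photons per millisecond is not a grade. The reason given for the rank test therefore does not apply to one of the two measures it covers, and it conflicts with the article's own description of that measure.

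The practical consequence is that laser flare is analysed as a change compared by ranks. Its baseline value, collected at screening, enters only by subtraction. Subtraction is usually a less efficient use of a baseline than covariate adjustment, and the number of laser readings is already limited to equipped centres. Laser flare is also an automated measure in an open-label trial whose Study design section says that assessments other than visual acuity and CMT cannot be masked, so its precision is worth having.

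**Working it through.** **No flare figure to reproduce.** The article's sample size (128 evaluable, 142 randomised) concerns CMT only. It gives no SD, effect size, baseline correlation or power for flare. The inputs below are therefore assumptions, shown over a range.

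**Step 1: cost of ranking alone.** For normal data the large-sample efficiency of a Wilcoxon-type test relative to a t test is 3/π = 0.955, a loss of about 5%.

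**Step 2: cost of change without a covariate.** Let σ² be the variance of log flare at each time and r the correlation between baseline and M2.

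- Variance of the change: 2σ²(1 − r)
- Variance after baseline adjustment: σ²(1 − r²)
- Ratio: (1 − r²) / [2(1 − r)] = (1 + r)/2

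| r (assumed) | Variance ratio (1 + r)/2 | Sample ratio, covariate only: 1/ratio | Sample ratio, covariate and ranking: 1/(ratio × 0.955) |
|---|---|---|---|
| 0.3 | 0.65 | 1.54 | 1.61 |
| 0.5 | 0.75 | 1.33 | 1.40 |
| 0.7 | 0.85 | 1.18 | 1.23 |

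Ranking alone corresponds to 1/0.955 = 1.05. On these large-sample figures, most of the 1.2 to 1.6 comes from the missing covariate.

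**Step 3: simulation.** The settings were 7 equipped centres of 10 patients each, an effect of 0.5 SD, two-sided 5% tests and 2,000 replicates. The linear models used centre indicators. All settings are assumptions, though 10 per centre is close to 142/14. Power at r = 0.3 / 0.5 / 0.7:

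| Analysis | Normal data | Lognormal data |
|---|---|---|
| Van Elteren on change (raw scale) | 0.36 / 0.46 / 0.71 | 0.37 / 0.45 / 0.67 |
| Linear model on change (raw scale) | 0.41 / 0.52 / 0.76 | 0.30 / 0.36 / 0.53 |
| Baseline-adjusted, raw scale | 0.57 / 0.63 / 0.81 | 0.38 / 0.44 / 0.56 |
| Baseline-adjusted, log scale | not applicable | 0.56 / 0.66 / 0.82 |

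- With normal data, ranking costs about 5 power points here, and 2 to 6 points when the 14-centre runs are included. That is somewhat more than the large-sample 5% suggests, because ranks are formed within small centres.
- Adding the covariate to the linear model on change gains 0.57 − 0.41 = 0.16, 0.63 − 0.52 = 0.11 and 0.81 − 0.76 = 0.05. The covariate is the larger part at r = 0.3 and 0.5, and about equal to the ranking loss at r = 0.7.
- With lognormal data, Van Elteren beats the linear model on raw change by about 7 to 14 points and roughly equals or beats raw-scale adjustment. Log-scale adjustment is ahead of all of them.
- Baseline adjustment on the suitable scale gains about 11 to 20 points over Van Elteren with 7 centres, and about 3 to 23 points with 14.

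**The case against.** The strongest reply is that nothing here is invalid. A Van Elteren test is legitimate for a continuous outcome, respects the stratification by centre, and is a cautious choice when the distribution is unknown. If flare is skewed, it does better than an untransformed linear model on change. All of that stands. A reader might infer that the rank test is itself wrong or wasteful, but neither the article nor the arithmetic supports that.

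A reader might also infer that baseline is ignored. It is not: the endpoint is a reduction from inclusion, so baseline is subtracted. What is not stated is its use as a covariate.

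Nor does the article support saying that flare will yield a p-value with no effect size. Statistical methods names a test but does not rule out an estimate, and Secondary outcomes foresees arm means at each visit.

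Finally, covariates for secondary models may be set in the full protocol or analysis plan, which are not shown, and the article states no baseline covariate for the other secondary endpoints either. That limits the point but does not remove it. For flare the article goes beyond silence: it fixes a test and gives a reason that does not fit the laser measure.

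**Conclusion.** The point holds as a cheap improvement, not as an error that threatens a conclusion. One label covers two different kinds of measurement, and it leads laser flare to an analysis that uses its baseline less efficiently than it could.

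The size depends on assumptions the article cannot confirm: log flare roughly normal, equal variance at baseline and M2, and a correlation of 0.3 to 0.7. Under these, baseline adjustment brings the variance to 65 to 85% of that of a change score. Including the large-sample ranking loss, this is equivalent to 1.2 to 1.6 times as many patients. The gain needs both the covariate and a suitable scale; adjusting raw, skewed readings would bring little or nothing over the planned test. The number of equipped centres is not given, so the effect on final precision cannot be stated.

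Laser flare is an optional measurement within one secondary outcome, with no power claim attached. The CMT non-inferiority result is untouched.

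**What to change.** Split the flare sentence in Statistical methods.

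- **Slit-lamp flare:** keep the Van Elteren test and the semiquantitative label.
- **Laser flare:** analyse log laser flare at M2 in a linear mixed model with baseline log flare as covariate and centre as random effect, the form already used for CMT. Report the back-transformed ratio between arms with its 95% CI. Keep the Van Elteren test as a check.

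The same edit should make the flare comparison agree with Secondary outcomes, which names arm means at each follow-up visit where Statistical methods names one rank comparison to 2 months.

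The cost is one additional model. It needs no new data, since a change score already requires both readings. The downside is reliance on roughly normal residuals after the log transform, which the retained rank test helps to guard against.

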**Methods:**

This protocol is therefore designed to compare the efficacy and safety of peri- and intraocular corticosteroid injections in the treatment of inflammatory macular oedema. In this ongoing study, 142 patients will be included, and the oedematous eye will be randomised to treatment with either subconjunctival triamcinolone injection or an intravitreal implant containing 700 μg dexamethasone. Follow-up is planned for 6 months with monthly visits. Each visit will include visual acuity measurement, a slit lamp examination, fundoscopy, intraocular pressure measurement, laser flare measurement (if available) and spectral domain optical coherence tomography.

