#### Follow-up visits

The monthly follow-up visits (M1–M6) allow for early detection of efficacy and complications (including ocular hypertonia) beginning within approximately 1 month [12, 23]. In addition, they provide reassurance for the patient and reduce protocol deviations and patients lost to follow-up.

The investigating physician will record any AEs/SAEs and any concomitant medications.

They will include the following in their examinations of the patient during visits M1, M2, M3, M4, M5 and M6 (visits M1 and M4 do not form part of the usual care): 1) measurement of CMT (by OCT); 2) measurement of visual acuity (using the ETDRS scale); 3) measurement of IOP; 4) examination of the anterior segment (by SL) for flare and crystalline lens clarity; 5) examination of the posterior segment (fundus) and nonmydriatic fundus photography for posterior vitreous haze; and 6) automated measurement of the flare (by LFM), if available. In addition, the patient will complete the EQ-5D questionnaire.

At M3 and M6, the patient’s blood pressure will be taken. A fluorescein angiograph is conducted at M2 and M6 if anomalies were detected at the inclusion visit. In addition, a blood sample will be taken at M6 to evaluate haemoglycaemia and fasting plasma glucose.

In cases of inadequate response or relapse between the M3 visit and the M6 visit, the investigator will be free to choose the appropriate treatment on the day that the inadequate response/relapse is detected, or later (± 30 days), at their discretion; follow-up visits will continue according to the initial schedule, i.e. monthly visits.

The research may be discontinued as a result of: 1) the patient withdrawing their consent; 2) necessity as decided by the investigator in case of SAEs that prevent the patient from continuing with the protocol; or 3) a decision by the authorities or the suspension/withdrawal of the drugs from the market.

In case of premature discontinuation from the study, the patient will be referred immediately to the investigator for a consultation to provide care for their disease. The premature end of study visit will be completed during this consultation.

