### Adverse event management

There are no pharmacokinetic data in the literature for triamcinolone administered subconjunctivally. The clinical experience of the various centres performing these injections shows a duration of action of approximately 3 to 4 months for 0.3 and 0.4 ml, respectively. The duration of action of an intravitreal injection of a dexamethasone 700 μg implant is approximately 3 to 6 months.

Inflammatory macular oedema, a chronic and recurrent pathology, requires regular ophthalmological monitoring at least every 6 months, regardless of the type of treatment administered.

The most frequently occurring adverse reactions identified based on the summary of product characteristics for Ozurdex® and the experience of the University Hospital of Nantes for triamcinolone are: 1) corticosteroid-induced hypertension (eye tone will be monitored monthly until the effectiveness of any injected corticosteroid has been exhausted and at longer intervals thereafter based on blood pressure control); and 2) cataract (the visual acuity and appearance of the lens will be monitored using an SL during the usual follow-up consultations for inflammatory macular oedema until cataract surgery is performed).

All the AEs encountered that are observed by the investigator or reported by the subject during the study, whether or not they are expected (see the summary of product characteristics for Ozurdex®), should be documented in the AE section of the CRF.

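### Duration of action is a time to relapse cut off at M6, but the Van Elteren test chosen for it cannot use censored values and relapse-free eyes are given no value

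*Protocol article*

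**What the plan says.** The protocol article's Objectives and Secondary outcomes sections both define duration of action by the return of oedema on OCT. Statistical methods then fix the analysis: "Duration of injection efficacy (duration is determined by the reappearance of oedema) will be compared between the groups using the Van Elteren test", and label the outcome semiquantitative. The same paragraph sets the missing-data rule: "There will be no imputation for missing data for these secondary end points".

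The observation window is in the abstract: "Follow-up is planned for 6 months with monthly visits". The Adverse event management section gives the expected durations. For triamcinolone, clinical experience "shows a duration of action of approximately 3 to 4 months for 0.3 and 0.4 ml, respectively". For the comparator: "The duration of action of an intravitreal injection of a dexamethasone 700 μg implant is approximately 3 to 6 months". The Background reports a real-life range of 4 to 5.9 months for the implant.

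Under Follow-up visits, for inadequate response or relapse between M3 and M6, "the investigator will be free to choose the appropriate treatment on the day that the inadequate response/relapse is detected", or within a further 30 days, and the monthly visits continue.

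The article gives no value, rank or censoring time for an eye that has not relapsed by M6, an eye lost before relapse, an eye whose oedema never cleared, or an eye retreated for inadequate response.

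**The concern.** A Van Elteren test is a stratified rank test. It needs one rankable value per eye and has no means of using the information that an eye was still dry when observation stopped. As defined, duration has a value only once oedema returns. The implant's expected range reaches the end of follow-up and triamcinolone's does not, so relapse-free eyes are likely to be more frequent in the implant arm.

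If those eyes are treated as missing, the best results are removed, and more of them from the longer-acting arm. What remains is a comparison among eyes that relapsed within six months, in which both arms look alike by construction. A null result could then be misread as similar duration. This matters because the primary end point is read at M2, and duration is the listed outcome that speaks to how long the effect lasts.

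**Working it through.** **The plan's own figures.** No power figure is given for duration. The sample size for the primary end point reproduces. The normal formula gives 2 × (1.960 + 0.842)² × (0.12/0.06)² = 62.8, so 63 per arm. The t-based version gives 64 per arm, hence the stated 128. With 10% missing, 128/0.90 = 142.2, against the stated 142. It is not in dispute.

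**Inputs from the article.** 142 eyes allocated 1:1, 14 centres as strata, monthly detection, cut-off at M6, and duration ranges of 3 to 4 and 3 to 6 months.

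**Assumptions.** Weibull durations with shape 2; medians picked from within those ranges; 10% dropout at a random visit; centres of equal size. The article states a 10% missing-data allowance only for M2; applying it to duration is an assumption.

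**Step 1: eyes relapse-free at M6.** With median m and shape 2, the share still relapse-free at 6 months is 0.5^((6/m)²).
- m = 3.5: 13%; m = 4.5: 29%.
- m = 4: 21%; m = 6: 50%.

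After adding dropout, the shares with no observed relapse are about 18% v 34% for medians of 3.5 v 4.5, and about 26% v 54% for 4 v 6.

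**Step 2: the difference that survives.** At shape 2 the mean is 1.064 × the median, so medians of 3.5 v 4.5 imply a true mean difference of 1.06 months. Among eyes with an observed relapse the simulated means are 3.66 v 3.95, a difference of 0.29 month.

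**Step 3: power under three treatments of the same data** (two-sided 5%, 1,500 simulated trials, Monte Carlo error about 0.01).

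| Medians, triamcinolone v implant | Van Elteren, relapsed eyes only | Van Elteren, relapse-free at M6 as top category | Centre-stratified log-rank |
|---|---|---|---|
| 3.5 v 4.5 | 0.17 to 0.18 | 0.62 | 0.68 |
| 4 v 6 | 0.16 | 0.93 | 0.95 |
| 4 v 4 | 0.05 | 0.05 | 0.04 |

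With the top category, the eyes still excluded (lost before relapse) are about 7% v 8% in each unequal scenario, nearly balanced between arms.

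**Step 4: sensitivity to the assumptions.** With shape 2.5 and no dropout, the three powers in the same order are 0.36, 0.87 and 0.90 for medians of 3.5 v 4.5; 0.18, 0.76 and 0.81 for 4 v 5; and 0.32, 0.99 and about 1.00 for 4 v 6. The pattern is the same.

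**Step 5: eyes that never clear.** The Sample size section reports log CMT 0.15 ± 0.08 at M1 after triamcinolone. That is 250 × 10^0.15 = 353 μm, above the 320 μm entry threshold. If clearing meant falling below 320 μm (an assumption; the article gives no threshold for reappearance), log10(320/250) = 0.107 and (0.15 − 0.107)/0.08 = 0.54, so on a normal approximation about 70% of such eyes would not have cleared at M1. Eyes with no defined reappearance may therefore not be rare. Which arm they would favour is unknown.

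**The case against.** The strongest reply is that nothing in the article says relapse-free eyes are excluded. Calling the outcome semiquantitative fits ordered categories by visit, and an eye seen dry at M6 has an observed result, not a missing one, so the no-imputation rule need not touch it. On that reading a centre-stratified rank test is a normal choice and most of the power loss disappears (0.62 v 0.68; 0.93 v 0.95). This stands. A reader might infer that the plan compares only eyes that relapsed; the documents do not say so, and that is only the less favourable of two open readings.

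Three further points also stand.
- A reader might infer that every retreated eye loses its duration. Retreatment for relapse follows a detected relapse, so those eyes have a date. Only eyes retreated for inadequate response are unclear.
- A reader might infer that duration is where the two products should differ most. No section says that, and the stated ranges overlap.
- Mean CMT is also compared at each visit, so waning of effect can be seen without a duration value.

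It can also be said that coding rules belong in the analysis plan. That is true of detail, but the article has already fixed a test that cannot use censored values for an outcome expected to be censored, and has barred imputation. An analysis plan that follows it inherits the problem unless it adds a category that the article does not mention.

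**Conclusion.** The point holds as a poor choice of analysis for one secondary end point; the primary M2 non-inferiority conclusion is untouched. Its size depends on how relapse-free eyes are coded. If they have no duration, the comparison is pulled towards no difference and power falls to about 0.18, where a stratified log-rank test would have about 0.68 (medians 3.5 v 4.5 months). If they form a top category, the loss is small (about 0.62). Even then, eyes lost before relapse drop out, and never-cleared eyes and eyes retreated for inadequate response have no defined value. Type I error stays near 5% in every case, so the risk is a missed difference, not a false one. The medians, Weibull shape and dropout rate are assumptions; the medians lie within the article's stated ranges.

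**What to change.** Analyse time to reappearance of oedema with a log-rank test stratified by centre, or a discrete-time or interval-censored model to respect the monthly visits, and show Kaplan-Meier curves. Censor relapse-free eyes, including those lost to follow-up, at their last OCT. Prespecify how never-cleared eyes and eyes retreated for inadequate response count in the analysis, for example as failures, with a sensitivity analysis under another convention.

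At the least, keep the Van Elteren test but state an explicit top category for eyes relapse-free at M6.

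The cost is analysis wording, settled before the data are analysed, and standard SAS procedures. The monthly OCT measurements needed are already in the visit schedule.
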